### MIRT-Based CAT Development

To capture the latent structure of symptoms appropriately, a bifactor multidimensional framework is outright adopted for model calibration. Within this definitive framework, all items load directly onto a single general internalizing factor while simultaneously contributing to independent, disorder-specific factors corresponding to MDD, GAD, SoPh, and PTSD. Model fit for this bifactor configuration will be rigorously assessed by evaluating the strength and significance of item factor loadings, examining global fit statistics, specifically the limited-information M2 statistic alongside absolute and relative indices such as the root mean square error of approximation and the comparative fit index, and visually inspecting observed versus expected item response plots to identify localized areas of measurement.

*DISC-5* symptom items in the K-NAMHS dataset are recorded as binary (yes/no) responses, indicating the presence or absence of specific symptoms. Item parameters will therefore be estimated using dichotomous item response theory models, allowing estimation of item discrimination and severity parameters for each symptom indicator. The baseline MIRT bifactor calibration will be executed via a stochastic expectation-maximization algorithm. To ensure population representativeness, normalized complex survey weights will be integrated directly into the estimation process to scale individual contributions to the marginal likelihood. Missing data handling strategies will differ by analytical phase. For the core MIRT calibration, missingness will be accommodated via full-information maximum likelihood, which leverages all available structural information without data loss. However, because post hoc adaptive testing simulations within the MIRT-CAT framework require a complete matrix to execute through high-missingness skip patterns, model-based plausible value imputation will be utilized strictly to construct the complete simulation response bank.

Adaptive simulations will iteratively select items that maximize information at the current trait estimate and allow us to determine the extent to which the CAT reproduces information in the full item bank. Item administration within the CAT engine will cease when the SE of the general factor theta estimate falls below a specified precision threshold, which is optimized to maximize the posttest correlation coefficient with full-bank estimates. Alternatively, administration will stop when a maximum question cap is reached to minimize respondent burden, allowing us to balance measurement precision with assessment length.

Model performance and operational efficiency will be evaluated through post hoc adaptive simulations executed across the entire calibrated dataset, adhering strictly to established psychometric validation standards for multidimensional screening tools.

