### MODN

In parallel with the MIRT-based development, AfriCAT will also be implemented using a MODN architecture [27]. MODN is a modular neural network framework in which each symptom question functions as an independent module that updates diagnostic probability estimates sequentially as new information is obtained [27]. Rather than estimating a single latent trait, this approach models the evolving probability of specific diagnostic states, recalibrating predictions dynamically with each response. Unlike traditional latent trait models, MODN more closely mirrors the logic of a clinical consultation, in which information is gathered iteratively and diagnostic impressions are updated in real time.

A deep learning encoder module will be created for each question in the dataset. A deep learning decoder module will be created for each outcome. Missing data are accommodated by the modular architecture and are simply ignored.

Five-fold cross-validation will be performed on the training set to optimize the hyperparameters of the models. The final models will then be trained on the full training set with the optimal hyperparameters. All analyses will be performed using the trained models on the test set. Overfitting will be controlled by early stopping the training after increases in the validation loss and sanity-checking the loss curves.

To remedy the low prevalence of internalizing disorders, we will also train models that overweight positive diagnosis cases. As the survey weights do not substantially alter the prevalence of the internalizing disorders, the models trained using them are not expected to differ significantly and would be less representative of individual adolescents. We will therefore not use the survey weights.

The model achieving the best prediction performance using all the questions on the test set will then be selected. Different combinations of next-question-selection methods and stopping rules will be compared based on their predictive performance and efficiency. They will be compared against baselines using entropy-based methods as next-question-selection and the *DISC-5* diagnostic criteria satisfaction as the stopping rule.

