#### Secondary Outcomes

Secondary outcomes include evaluation of the adaptive assessment’s ability to estimate a general internalizing dimension alongside disorder-specific symptom domains, as well as assessment of model stability under internal validation procedures. For the MODN architecture, the calibration of probabilistic outputs will be assessed using calibration curves and the expected calibration error metric. The interpretability of sequential prediction updates will be represented as heatmaps and will be qualitatively assessed for potential integration into routine provider workflow.

For the DCE, outcomes will include estimation of relative attribute importance and trade-offs between implementation features. Preference heterogeneity by country and age group will also be explored. Quantitative surveys within the second workshops with adolescents will explore feasibility, acceptability, and appropriateness of the AfriCAT tool using validated scales [43]. For the qualitative components, outcomes will include identification of themes related to acceptability, feasibility, appropriateness, and alignment with stepped-care frameworks.

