## Discussion

### Expected Outcomes

The primary expected outcome of AfriCAT is the development and internal validation of a computerized adaptive assessment for adolescent depression and anxiety calibrated using nationally representative Kenyan adolescent mental health data. Subsequent research will evaluate the transportability and performance of the adaptive assessment in other African settings. The study will generate new knowledge regarding the dimensional structure of internalizing symptoms in Kenyan adolescents, the feasibility of adaptive assessment within this context, and the comparative performance of MIRT-based and modular neural architectures for mental health evaluation. By integrating psychometric modeling with participatory co-design and quantified preference elicitation, the study will also contribute methodologically to the emerging field of digital mental health in LMICs.

Beyond advancing psychometric science, AfriCAT is intended to serve as foundational infrastructure for measurement-based adolescent mental health care. The adaptive engine is designed to support identification of clinically significant symptoms, stratification within stepped-care models, and longitudinal monitoring of treatment response. In resource-constrained systems, where specialist capacity is limited and task-shared models are required, efficient and precise assessment tools are essential for optimizing allocation of care. By reducing assessment burden while maintaining measurement precision, AfriCAT has the potential to support scalable screening and monitoring without overwhelming services.

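### With one prespecified bifactor model and no comparator, the study can describe a bifactor solution but cannot show it is better supported than rival structures, so its claim on dimensional structure goes too far

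*Protocol article*

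**What the plan says.** The section MIRT-Based CAT Development commits to one structure: "a bifactor multidimensional framework is outright adopted for model calibration". It specifies the factors: "Within this definitive framework, all items load directly onto a single general internalizing factor while simultaneously contributing to independent, disorder-specific factors" for MDD, GAD, SoPh and PTSD.

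The checks concern that model alone: "Model fit for this bifactor configuration will be rigorously assessed by evaluating the strength and significance of item factor loadings", then "the limited-information M2 statistic alongside absolute and relative indices such as the root mean square error of approximation and the comparative fit index", then plots of observed against model-predicted item responses. The nearest hint of further models is one adjective: "The baseline MIRT bifactor calibration will be executed via a stochastic expectation-maximization algorithm". No later or alternative model is named anywhere in the article.

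Under Expected Outcomes the Discussion states: "The study will generate new knowledge regarding the dimensional structure of internalizing symptoms in Kenyan adolescents". The Secondary Outcomes section lists the "ability to estimate a general internalizing dimension alongside disorder-specific symptom domains".

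**The concern.** Knowledge of dimensional structure normally means evidence for one arrangement of factors over plausible others. The obvious others here are a single internalizing dimension, four correlated disorder factors, and four disorder factors under a second-order factor. The plan fits none of them. The comparative fit index is a relative index, but it compares the model with a baseline model, not with a competing structure.

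The neural architecture does not fill the gap. The MODN section says of it: "Rather than estimating a single latent trait, this approach models the evolving probability of specific diagnostic states". The Primary Outcomes section rules out a head-to-head comparison of the two approaches.

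At stake is mainly what may be concluded about structure. There is also a link to the adaptive engine. Testing stops on the standard error of the general factor or at an item cap, and the precision threshold is tuned to agreement with full-bank estimates. Those estimates come from the same bifactor calibration, so high agreement is not evidence for the structure.

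**Working it through.** The article gives no figure to reproduce on this point. The check has three steps.

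**1. What nesting does and does not give.** In a second-order model, let item *i* of domain *d* load λᵢ on its domain factor, and let that factor load γ_d on the general factor. Then the item's general loading is λᵢγ_d and its specific loading is λᵢ√(1 − γ_d²). This is a bifactor model whose general-to-specific ratio is constant within each domain. The bifactor's maximised likelihood is therefore never below the second-order model's. The one-factor model is also nested, with all specific loadings zero. The correlated four-factor model with free correlations is not nested in the bifactor in general, so for that rival the question is how closely a bifactor can imitate it.

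**2. An illustration of how closely.** The inputs are assumptions, not document figures: 4 domains of 8 items (32 items), loadings between 0.55 and 0.85, a linear factor model standing in for the planned dichotomous model, and population-level maximum likelihood without sampling error.

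- Distinct covariance elements: 32 × 33 / 2 = 528.
- Bifactor: 64 loadings + 32 unique variances = 96 parameters, so df = 528 − 96 = 432.
- One factor: 32 + 32 = 64 parameters, so df = 528 − 64 = 464.
- RMSEA = √(F/df). CFI = 1 − F/F_baseline. General-factor share (explained common variance, ECV) = sum of squared general loadings / sum of all squared loadings.

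| True structure | Model fitted | F | RMSEA | CFI | General share |
|---|---|---|---|---|---|
| (a) Four factors, all correlations 0.6 | Bifactor | 0.00000 | 0.000 | 1.000 | 0.60 |
| (a) | One factor | 4.01076 | √(4.01076/464) = 0.093 | 0.719 | – |
| (b) Four factors, correlations 0.35 to 0.75 | Bifactor | 0.04032 | √(0.04032/432) = 0.010 | 0.997 | 0.58 |
| (b) | One factor | 4.51482 | √(4.51482/464) = 0.099 | 0.684 | – |
| (c) One factor | Bifactor | 0.00000 | 0.000 | 1.000 | 1.00 |
| (c) | One factor | 0.00000 | 0.000 | 1.000 | – |

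Case (a) is exactly a second-order structure with γ² = 0.6, which is why the bifactor is exact and the general share is 0.60. Case (b) is not second-order: the products of opposite correlations are 0.75 × 0.35 = 0.2625, 0.45 × 0.55 = 0.2475 and 0.60 × 0.60 = 0.36, and a second-order model would need them equal. The bifactor's RMSEA and CFI still look excellent there.

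**3. Reading the planned output.** In all three cases RMSEA and CFI would be reported as very good. The loadings add something: the general share separates (c), at 1.00, from (a) and (b), at 0.60 and 0.58. They do not separate a true bifactor from a second-order or correlated-factor structure, since a share near 0.6 is compatible with each. As a significance test, M2 could be sensitive to a departure like (b): on the linear proxy, 5155 × 0.04032 ≈ 208 would be added to an expected chi-square of 432, ignoring weights and clustering. It would stay silent in (a). Where it did reject, it would say the bifactor is not exact without saying which structure is better.

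**The case against.** The case on the other side is substantial.

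- **The planned output carries structural information.** Negligible specific factors would appear as negligible specific loadings, and a weak general factor as weak general loadings. M2 and RMSEA can reject the bifactor in absolute terms; nesting guarantees only relative fit. This stands. A reader might infer that the study can learn nothing about dimensionality, or could not detect a collapsed factor. The documents do not support that.
- **Fixing the structure is legitimate for building an adaptive test.** The Item Bank Development section gives a rationale in symptom overlap and comorbidity, and none of the five objectives is to test dimensionality. This stands too. A reader might infer that the engine rests on a wrong structure. Nothing in the article shows that. Testing also stops at an item cap, MODN uses no latent factor, and classification is judged against diagnoses for each disorder.
- **The secondary outcome is not a structural test.** It concerns estimation within the chosen model, so it does not itself conflict with the plan. The tension lies with the Discussion sentence, and to a lesser degree with the stated purpose of capturing the latent structure.
- **Comparators may be detail left to a fuller plan.** This does not stand. The article does more than stay silent: it declares the structure adopted and definitive and ties the fit assessment to that configuration.
- **It may be late.** The Results section reports the psychometric modeling component as complete, but also says calibration is underway and simulation is still to come. Extra fits to data in hand remain feasible.

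**Conclusion.** The point holds in a limited form. Under the stated analysis, the study can describe general and specific loadings under an assumed bifactor model and can detect gross failure of that model. It cannot show that the bifactor is better supported than a correlated four-factor or second-order structure. The Discussion sentence on dimensional structure goes further than that.

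The size cannot be computed from the article. The illustration shows the direction only: near-perfect bifactor fit (RMSEA at most 0.010, CFI at least 0.997) under correlated-factor truths. It rests on invented loadings, 32 items and a linear proxy. The nesting result for the second-order model does not depend on those choices. Severity is minor: the adaptive engine can proceed, and what changes is the conclusion that may be drawn about structure.

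**What to change.** In MIRT-Based CAT Development, add one-factor, correlated four-factor and second-order calibrations to the same training data with the same survey weights. Then:

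- Compare all four models by log-likelihood on the held-out 20% described under Analysis. This requires each model, the bifactor included, to be calibrated on the training 80% for the comparison.
- Report information criteria as well, noting that with survey weights they rest on a pseudo-likelihood and should be read with caution.
- Report the bifactor's explained common variance and omega-hierarchical, because fit indices alone tend to favour the bifactor.
- Keep the bifactor as the working model for the adaptive test, and word the Discussion claim to match what the comparison shows.

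If no comparison is run, limit the Expected Outcomes sentence to something such as: the study will describe how strongly symptoms load on general and disorder-specific factors under an assumed bifactor model.

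The cost is three more calibrations on data already in hand, with no new participants. The downside is that a rival fitting as well or better would have to be reported. The narrower wording alone costs nothing. This is a cheap improvement.

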### Outcomes

#### Primary Outcomes

Because MIRT and MODN estimate fundamentally different quantities, namely severity and probability of diagnosis, they cannot be meaningfully compared head-to-head. Instead, we will review the relative strengths and limitations of the models in supporting measurement-based mental health care. Primary metrics of evaluation will include (1) precision of severity estimation across internalizing symptom dimensions; (2) efficiency, operationalized as the median number of items required to achieve stable estimates or certain predictive performance; and (3) diagnostic classification performance relative to *DSM-5* diagnoses for MDD, GAD, SoPh, and PTSD. Diagnostic classification performance will be evaluated using established metrics such as sensitivity, specificity, and area under the receiver operating characteristic curve. To assess fairness across age and gender, each outcome will be computed for each subgroup and compared.

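### The MIRT-CAT's only precision stopping criterion is the general-factor SE, so the stated rule does not secure the disorder-level precision and classification that are primary metrics

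*Protocol article*

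**What the plan says.** All of this is in the protocol article.

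- **Model** (MIRT-Based CAT Development): a bifactor model in which every item loads on one general internalizing factor while "simultaneously contributing to independent, disorder-specific factors corresponding to MDD, GAD, SoPh, and PTSD". Items are "recorded as binary (yes/no) responses".
- **Item selection** (same section): "Adaptive simulations will iteratively select items that maximize information at the current trait estimate". The text does not say whether this means information on the general factor or on all factors jointly. No content balancing is stated.
- **Stopping** (same section): item administration "will cease when the SE of the general factor theta estimate falls below a specified precision threshold". Alternatively, "administration will stop when a maximum question cap is reached to minimize respondent burden". Neither the threshold nor the cap has a value.
- **Tuning the threshold** (same section): "which is optimized to maximize the posttest correlation coefficient with full-bank estimates". Which factor's estimates are meant is not said.
- **Primary Outcomes**: metric 1 is "precision of severity estimation across internalizing symptom dimensions", metric 2 is efficiency in number of items, and metric 3 is classification against the four DSM-5 diagnoses.
- **Secondary Outcomes**: the assessment's "ability to estimate a general internalizing dimension alongside disorder-specific symptom domains" is evaluated.

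**The concern.** The rule that decides when a simulated test has enough information looks at one dimension. The results are then judged on that dimension and four more. With independent specific factors, a small general-factor SE guarantees nothing about the precision of the MDD, GAD, SoPh or PTSD factor. The question cap limits length and protects no module either.

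If a test ends before a module is sampled, that module's specific score stays at its prior mean, and the disorder is judged on general distress only. A weak MIRT result on metrics 1 or 3 could then come from the stopping rule rather than from the item bank or the model. That would blur the appraisal of the two engines promised in Primary Outcomes. The MODN section, by contrast, plans to compare several stopping rules.

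**Working it through.** **Inputs.** From the article: one general and four specific factors, binary items, an SE criterion on the general factor, a cap, and selection by maximum information. Not in the article: the threshold, the cap, the bank size, the loadings, the item severities and the type of information. There is therefore no plan figure to reproduce.

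**Step 1: a module with no item.** Let g be the general factor and s_k the specific factor of module k, independent and N(0,1) a priori (the usual bifactor reading). If no item of module k has been answered, the likelihood does not contain s_k. Hence p(s_k | responses) = p(s_k) and SE(s_k) = 1.00, whatever SE(g) is. The precision criterion can be met with a specific factor wholly unmeasured.

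**Step 2: what the general factor still supplies.** The specific share of a module's common variance is λ_s² / (λ_g² + λ_s²). For the three loading pairs assumed below:
- 0.5/0.5: 0.25 / 0.50 = 50%
- 0.6/0.4: 0.16 / 0.52 = 31%
- 0.7/0.3: 0.09 / 0.58 = 16%

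The general score carries the rest of the disorder's severity. This share can come only from the module's own items.

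**Step 3: how often a module is skipped (main grid).** All settings are assumptions: 4 modules of 15 binary 2PL items; the loadings above; mean item threshold +1.0 SD; general loadings equal across modules or differing by up to ±0.08; three readings of maximum information (general-factor Fisher information, Bayesian D-rule, largest fall in general-factor variance, or Ds); 1,600 simulees per cell. Share of tests with at least one module never asked:

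| SE threshold / cap | Share |
|---|---|
| 0.3 / 30 | 0–11% |
| 0.4 / 12 | 0–48% |
| 0.4 / 30 | 0–44% |
| 0.5 / 12 | 0–65% |
| 0.5 / 30 | 0–62% |

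Some misses come from the cap. With loadings 0.5/0.5, unequal modules, general information and cap 12, 34% miss a module although at most 1% reach the SE threshold.

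A separate run (another assumed 60-item bank, cap 20) gave 39%, 27% and 10% at thresholds 0.50, 0.45 and 0.40, and 72%, 45% and 9% with an easier bank. The figure depends heavily on inputs that the article does not state.

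**Step 4: precision when every module is sampled.** Under the D-rule (0.6/0.4, equal modules, SE 0.5, cap 30), 0% miss a module. Mean specific-factor SE is still 0.83, against 0.74 for the full bank and 1.00 for the prior. Sensitivity is 0.61 against 0.79 for the full bank. Here a diagnosis is the top 5% of general-plus-specific liability, and the top 5% of scores are flagged.

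**Step 5: effect of a per-module minimum.** With at least 3 items per module before the SE rule may act (cap 30, unequal modules):

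| Rule, loadings, SE | Missing a module | Median items | Sensitivity |
|---|---|---|---|
| General information, 0.6/0.4, 0.5 | 45% → 0% | 10 → 15 | 0.56 → 0.65 |
| General information, 0.7/0.3, 0.5 | 62% → 0% | 5 → 12 | 0.56 → 0.73 |
| General information, 0.7/0.3, 0.4 | 44% → 0% | 10 → 14 | 0.63 → 0.74 |
| Ds, 0.6/0.4, 0.5 | 27% → 0% | 8 → 12 | 0.50 → 0.62 |
| Ds, 0.6/0.4, 0.4 | 0% → 0% | 29 → 29 | 0.61 → 0.63 |
| Ds, 0.7/0.3, 0.5 | 58% → 0% | 5 → 12 | 0.57 → 0.73 |
| Ds, 0.7/0.3, 0.4 | 33% → 0% | 9 → 13 | 0.62 → 0.72 |

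With a minimum of 2 items in the separate run, mean length moved from 9.8 to 11.3 at threshold 0.50 and from 14.6 to 14.3 at 0.40. At 0.50, the worst module's correlation with its symptom count rose from 0.69 to 0.80.

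**The case against.** The strongest reply has four parts.

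- **This is a condensed article.** Numerical thresholds and content balancing are commonly left to the full plan. That excuses the missing values. It does not remove the mismatch: the article states which dimension the precision criterion uses, and it differs from what the primary metrics assess.
- **Classification may belong mainly to MODN.** Primary Outcomes associates MIRT with severity and MODN with probability of diagnosis, and Prototype Development allows hybrids. But metric 1 concerns severity across dimensions, which is MIRT's task, and the study objectives promise diagnostic classification for the adaptive assessment without excepting MIRT.
- **Tuning to full-bank agreement favours a strict threshold.** This stands. In the separate run the general-factor correlation rose from 0.93 to 0.97 as the threshold fell from 0.50 to 0.40, and at SE 0.3 with cap 30 few tests skip a module. The cap may then end many tests, and it secures no module.
- **Weak recovery would be seen.** Secondary Outcomes evaluates the specific domains, and the prototypes are for research only. This limits the harm, but evaluating the domains afterwards does not let them govern stopping.

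A reader might go further and infer that many tests will end without a question from some module, that the SE rule acts alone, that tuning uses only the general factor, or that the engine could not support disorder-level triage. The documents support none of these. The skipping rate cannot be derived, there is a cap, the full-bank estimates used for tuning are not identified, and the general factor carries part of each disorder's severity.

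**Conclusion.** The point holds as a mismatch between a stated rule and the stated primary metrics. It follows from the text and from the independence of the specific factors, and needs no simulation. Its size is uncertain: 0% to about 65% of tests skip a module over the main grid, with one easier-bank run at 72% and only 0% to 11% under a strict threshold with a long cap. These figures illustrate what can happen under assumed banks and do not predict this study's result. A low skipping rate would not settle the matter, because specific-factor precision and sensitivity can fall well below the full bank with every module sampled. This is a worthwhile, inexpensive improvement and does not invalidate the design.

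**What to change.** Amend the stopping rule in MIRT-Based CAT Development so that, subject to the cap, a simulated test stops only when the general-factor SE criterion is met **and** either each of the four modules has contributed a small minimum number of items (for example 2) or each specific factor meets its own SE criterion. In addition:

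- state that the threshold is tuned on disorder-level as well as general-factor agreement with full-bank estimates;
- run the simulations with and without the constraint;
- report the SE at stopping for all five dimensions and the share of tests with no item from each module.

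If stopping on the general factor is intended, say so and limit the disorder-level claims for the MIRT engine accordingly.

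**Cost.** The change needs wording and simulation runs but no new data. The article's Results section places simulation-based validation after calibration, so the change can still be made in time. The real downside is length, which counts against primary metric 2. In the cases simulated it was about 0 to 3 more items on average with a two-item minimum. With three items it was 4 to 7 more in the median wherever modules had been skipped. Reporting both versions lets the study show this trade-off.
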